# Health and economic effects from linking bedside and outpatient tobacco cessation services for hospitalized smokers in two large hospitals: study protocol for a randomized controlled trial

**DOI:** 10.1186/1745-6215-13-129

**Published:** 2012-08-01

**Keywords:** Smoking cessation, Hospitalized smokers, Assisted referral to outpatient services, Cost-effectiveness analysis, Randomized clinical trial

## Abstract

**Background:**

Extended smoking cessation follow-up after hospital discharge significantly increases abstinence. Hospital smoke-free policies create a period of ‘forced abstinence’ for smokers, thus providing an opportunity to integrate tobacco dependence treatment, and to support post-discharge maintenance of hospital-acquired abstinence. This study is funded by the National Heart, Lung, and Blood Institute (1U01HL1053231).

**Methods/Design:**

The Inpatient Technology-Supported Assisted Referral study is a multi-center, randomized clinical effectiveness trial being conducted at Kaiser Permanente Northwest (KPNW) and at Oregon Health & Science University (OHSU) hospitals in Portland, Oregon. The study assesses the effectiveness and cost-effectiveness of linking a practical inpatient assisted referral to outpatient cessation services plus interactive voice recognition (AR + IVR) follow-up calls, compared to usual care inpatient counseling (UC). In November 2011, we began recruiting 900 hospital patients age ≥18 years who smoked ≥1 cigarettes in the past 30 days, willing to remain abstinent postdischarge, have a working phone, live within 50 miles of the hospital, speak English, and have no health-related barriers to participation. Each site will randomize 450 patients to AR + IVR or UC using a 2:1 assignment strategy. Participants in the AR + IVR arm will receive a brief inpatient cessation consult plus a referral to available outpatient cessation programs and medications, and four IVR follow-up calls over seven weeks postdischarge. Participants do not have to accept the referral. At KPNW, UC participants will receive brief inpatient counseling and encouragement to self-enroll in available outpatient services. The primary outcome is self-reported thirty-day smoking abstinence at six months postrandomization for AR + IVR participants compared to usual care. Additional outcomes include self-reported and biochemically confirmed seven-day abstinence at six months, self-reported seven-day, thirty-day, and continuous abstinence at twelve months, intervention dose response at six and twelve months for AR + IVR recipients, incremental cost-effectiveness of AR + IVR intervention compared to usual care at six and twelve months, and health-care utilization and expenditures at twelve months for AR + IVR recipients compared to UC.

**Discussion:**

This study will provide important evidence for the effectiveness and cost-effectiveness of linking hospital-based tobacco treatment specialists’ services with discharge follow-up care.

**Trial Registration:**

ClinicalTrials.gov: NCT01236079

## Background

How health-care facilities treat tobacco dependence in patients with cardiac and pulmonary diagnoses is a quality-of-care measure that ultimately affects whether facilities meet accreditation standards [1]. The Joint Commission recently expanded the requirement that health-care facilities also treat tobacco dependence to patients with other diagnoses, and broadened the requirements for what constitutes effective treatment [2,3]. Efforts to establish tobacco cessation as an element of treatment required to meet inpatient standards of care capitalizes on the forced abstinence that occurs with a hospital stay in a smoke-free facility. Hospital stays can also potentially increase smokers’ motivation to remain quit if their illness and hospitalization is smoking-related. Previous research has shown that initiating professional treatment during this ‘teachable moment’, and providing patients with multiple intervention contacts after discharge, leads to significant increases in quit rates [3-10]. Smokers with four or more weeks of cessation support postdischarge are more likely to be abstinent after a year compared to those without support [7].

Creating an integrated clinical pathway—from inpatient assistance to outpatient cessation services—is challenging for any health-care delivery system, even closed-model HMOs that provide inpatient services as well as outpatient clinical care and behavior-change services. An effective model includes in-hospital treatment by trained professionals whose primary responsibility is tobacco cessation [10] and a hospital-managed follow-up program for continuity of care [11]. With the growing use of electronic medical records (EMR) to support medical decisions and document care, any tobacco-cessation model also should be able to establish an integrated clinical pathway, from admission through discharge instructions and follow-up, for health providers to order and document treatment and referrals. Integrating inpatient and outpatient cessation services is much more daunting for free-standing and academic hospitals that serve patients who are potentially covered by dozens of health insurance plans. Typically, insurance plans will cover inpatient services but prior authorization is needed for outpatient coverage. Creating an effective hospital-initiated treatment program requires an innovative solution to bridge the gap from inpatient to effective outpatient care that lasts at least four weeks postdischarge.

This paper describes the protocol for the Inpatient Technology-Supported Assisted Referral (I-TSAR) study. This randomized controlled trial evaluates the effectiveness and cost-effectiveness of an approach for initiating and integrating tobacco treatment into hospital care and continuing follow-up care for patients admitted to Kaiser Permanente Northwest (KPNW) and Oregon Health & Science University (OHSU) hospitals. This intervention uses existing electronic medical records systems and tobacco treatment specialists (TTS) (nurses and/or health educators) to identify smokers and deliver effective components of hospital-initiated treatment; provide proactive assisted referrals to available outpatient counseling programs and medications; and link patients to an innovative interactive voice recognition (IVR) telephone follow-up system. IVR follow-up represents a promising method for efficient postdischarge follow-up for treatment plans initiated during hospitalization [12-14]. Combining tobacco treatment expertise with health-system technology can help address many of the existing problems with integrating in-hospital tobacco-dependence treatment and cost-effective outpatient follow-up care.

## Methods/Design

This is a multicenter, randomized usual care-controlled clinical effectiveness trial conducted with patients admitted to two large hospitals serving the Portland, Oregon and southwest Washington metropolitan area. We will randomize 900 participants to receive either an inpatient assisted referral for postdischarge tobacco-cessation services plus interactive voice recognition support (AR + IVR) or usual care (UC). This study is one of six studies funded by the National Institutes of Health (NIH) that make up the Consortium of Hospitals Advancing Research on Tobacco (CHART). The study was approved by the Institutional Review Board (IRB) of each participating institution, and all participants provide written informed consent. The CHART Data Safety Monitoring Board (DSMB) also reviewed and approved the study.

### Setting

Participants will be recruited from KPNW Sunnyside Medical Center and OHSU hospital in Portland, Oregon. KPNW is a federally qualified, not-for-profit HMO serving more than 470,000 members in northwest Oregon and southwest Washington through one hospital and 26 medical offices. It is an integrated, group-model health-delivery system that provides and coordinates the entire scope of care for its members, including access to a range of tobacco-cessation services through its Health Education Department. Existing inpatient tobacco-cessation services encourage patients with pneumonia, chronic heart failure, and ischemic heart disease to quit and enroll in cessation services upon discharge. OHSU is an academic health center serving a multistate area with specialty tertiary health-care services. OHSU has an existing inpatient tobacco-cessation consult service provided to patients referred by hospital staff: the service includes encouragement to use outpatient cessation services and a single follow-up call shortly after discharge.

KPNW and OHSU have comprehensive EMR systems and have established tobacco-free campuses. In 2010, the Oregon legislature mandated that all Oregon commercial health insurance plans provide a $500 benefit for tobacco-cessation counseling and FDA-approved medications. Oregon’s Medicaid program already provides comprehensive coverage.

### Population

The study population consists of adult patients age ≥18 years admitted to KPNW or OHSU hospitals who have smoked a cigarette (even a puff) within the past 30 days, speak English, have a working telephone, are interested in attempting to remain abstinent from smoking postdischarge, and can participate in the informed consent process. Patients must also live within 50 miles of the hospital and be willing to attend an in-person follow-up visit at six months. Patients are excluded from the study if they are admitted to a critical care, labor/delivery, or psychiatric unit, are pregnant or breastfeeding, have access restrictions (for example, MRSA), are physically too ill to participate in a research study (that is, cannot complete a six-month follow-up), or are cognitively unable to provide informed consent. Patients with a history of mental illness are included if admitted to nonpsychiatric units.

The eligibility requirements well represent the population of hospitalized current smokers and very recent quitters who meet the Joint Commission targeted patient population. The Joint Commission’s tobacco treatment standards apply to all patients regardless of diagnosis, except the cognitively impaired [2], who would likely be interested in services to help them remain abstinent after they leave the hospital, and could benefit from enrollment assistance from hospital staff and brief telephone follow-up. The exceptions to this standard include women in labor/delivery units and patients who are unlikely to attend a six-month in-person follow-up assessment visit. This and other CHART studies define smoking eligibility as having smoked at least one cigarette in the last thirty days. This commonly used definition recognizes the likelihood that many patients may report quitting smoking even though they may have stopped within the couple of weeks prior to admission. The TTS will postpone a consult visit if a patient cannot speak, is heavily medicated, in obvious pain, or has restricted access. In some instances, we expect the TTS EMR review to indicate that a patient is too physically ill to participate, for example, the patient is documented with a severely life-limiting condition or is to be discharged to hospice care.

Administrative data show that more than 5,000 current adult smokers meeting the above eligibility requirements are discharged each year from KPNW and OHSU hospitals (Table1). The demographic characteristics of discharged smokers are similar between the two sites. Ethnicity and race are routinely collected at hospital admission at both institutions, although KPNW only recently began collecting this information. In 2010, data indicate that hospitalized smokers were predominantly non-Hispanic and white. According to the 2010 Census data, about 19.5% of the Portland, Oregon metropolitan area served by Kaiser Permanente and OHSU is of either non-white or mixed race and 10.9% are of Hispanic ethnicity. Consequently, our study will over-recruit Hispanic and other minorities in order to match the demographics of the surrounding community.

**Table 1 T1:** Characteristics of likely eligible smokers discharged from KPNW and OHSU hospitals in 2010

		**Kaiser Permanente Northwest**		**Oregon Health & Science University**	
**Patient characteristic**	**N**	**%**	**N**	**%**
**Total discharged smokers**	3401	100.0	2208	100.0
**Male**	1757	51.7	1142	51.7
**Age group**				
**18-24**	12	0.4	193	8.7
**25-34**	101	10.7	390	17.7
**35-44**	363	20.3	353	16.0
**45-54**	690	26.6	555	25.1
**55-64**	905	20.4	454	20.6
**65-74**	695	12.5	188	8.5
**75+**	211	6.2	75	3.4
**Ethnicity**				
**Hispanic/Latino**	74	2.2	77	3.5
**Non-Hispanic**	1919	56.4	2111	95.6
**Unknown**	1408	41.4	20	0.9
**Race**				
**White**	2700	79.4	1964	89.0
**Black/African American**	140	4.1	118	5.3
**Asian and Pacific Islander**	59	1.7	46	2.1
**American Indian/Alaska Native**	40	1.2	35	1.6
**Other**	32	0.9	24	1.1
**Unknown**	357	10.5	21	1.0
**Insurance plan type**				
**Commercial**	1899	55.8	578	26.2
**Medicare**	1264	37.2	554	25.1
**Medicaid/OHP**	95	2.8	645	29.2
**Nonsponsored**	101	3.0	332	15.0
**Other sponsored**	42	1.2	99	4.5

Discharge data also show that smokers were somewhat more likely to be male. Thus, our recruitment strategy incorporates a 50% female/male enrollment target.

### Recruitment

Participant recruitment involves an initial prescreening process using electronic administrative and medical records data at each site, followed by an in-person screening by the TTS at each site for patients who appear eligible during EMR prescreening. The EMR prescreening process allows the TTS to efficiently identify likely eligible patients and review relevant medical histories before an in-person consultation. The recruitment process is reflected in the I-TSAR consort diagram (Figure1).

**Figure 1 F1:**
[figure not shown]
I-TSAR consort diagram.

We will need to recruit about 12% of the estimated 6,250 adult smokers who meet our eligibility criteria in order to meet our recruitment target of 900 smokers over 15 months. Our experience with patient populations suggests that 50% or more of identified smokers will meet the study criteria and be interested in trying to quit [10], and 50% or more of these patients will be interested in participating in the study [3,9,10,15]. Thus, if we underachieve our recruitment goal by half we will still meet our recruitment target.

We expect a high follow-up rate for six- and twelve-month assessments. Studies of KPNW and OHSU patients typically achieve follow-up rates of 85% and above for clinical studies [10,15-17]. Each site employs experienced recruitment staff who use electronic tracking systems that collect and maintain up-to-date scheduling and contact information, notification of upcoming follow-up encounters, and web- and phone-based queries for missing addresses.

#### *EMR prescreening*

Each morning, information for admitted patients is captured from the EMR and downloaded into an electronic report used for prescreening. Patients are excluded if they are currently under age 18, have no recent smoking history, are located in one of the excluded units, or have already been screened for the study. Since the number of eligible smokers per day is likely to exceed the capacity of study staff, an algorithm is used to create a daily contact list that objectively assigns patients a contact order (1-n) for in-person screening and recruitment. The algorithm also incorporates recruitment targets for Hispanics, racial minorities, and females. Once the contact list is generated, the TTS reviews electronic records for additional exclusions. Decision making for physical and cognitive exclusions is guided by nurse and physician scope of practice at each site. The remaining prescreened eligible patients are contacted by the TTS for additional screening and recruitment is conducted as part of a tobacco-cessation consult. Patients on the contact list who are not seen by a TTS are re-prioritized the next day if they are still hospitalized.

#### *In-person screening and baseline assessment*

All patients contacted and willing to discuss tobacco use are provided a brief tobacco-cessation consult (see usual care description below). The TTS conducts face-to-face screening to confirm eligibility, assess interest in participation, conduct informed consent procedures, complete a baseline assessment, and randomize participants to the AR + IVR or UC groups.

### Randomization

Randomization is conducted using a selection and documentation procedure that ensures balanced enrollment over time, blinds the TTS to the assignment, and prevents postrandomization assignment changes. Each site randomly assigns 450 patients on a 2:1 ratio (300 AR + IVR: 150 UC) using secure, preprinted, sequentially numbered randomization envelopes. The study statistician developed a randomization algorithm using a predetermined randomization sequence with permuted blocks of randomly varying size. The block size is masked from all except the data coordinating center (DCC) statistician and programmer. This strategy ensures balanced enrollment over time and eliminates the ability of the TTS to guess assignment prior to randomization.

The randomization algorithm matches group assignment to a four-digit randomization number, where the first digit is the site ID (KP = 1; OHSU = 2) and the last three digits are the randomization sequence number. The randomization number is printed on a label and affixed to the outside of each randomization envelope. Inside each envelope are two identical self-adhesive labels printed with the randomization number and treatment arm assignment. The labels are used to confirm and track randomization. The envelopes are placed in a box in ascending order. The treatment arm assignment is not discernable from the outside of the sealed envelope.

Once a patient is prescreened eligible, the TTS selects the next randomization envelope in sequence, along with other patient enrollment forms, and proceeds to the patient’s room. After the eligible patient provides informed consent and completes baseline assessment, the TTS opens the randomization envelope and records the participant’s assignment. At the KP site, the TTS affixes one of the randomization labels to the site’s randomization log, and then records the date and time of randomization, the participant ID number, and the TTS’ initials on the log. A second label is affixed to the enrollment checklist form before transmission to data entry staff. At the OHSU site, the TTS opens the randomization envelope, places one of the randomization labels in the patient’s research chart, records the date and time of randomization, participant ID number, and the TTS’ initials. A second label is affixed to the enrollment checklist before transmission to KP data entry staff.

Randomization fidelity is monitored regularly by comparing information from the randomization log, prescreening priority list, and the consult and enrollment checklists. The fidelity review process involves comparisons of participants’ randomization dates and times, group assignments, and predetermined randomization numbers. Any unexpected deviation will be reported to the study principal investigator. Participant assignment fidelity is maintained during the study by restricted access to the file service containing randomization data to the study statistician and data analyst. Study investigators and follow-up staff are blinded to treatment group data.

All randomized patients will be included in the intention-to-treat analysis of the primary outcome. We use a 2:1 assignment strategy to increase the number of AR + IVR recipients in order to enhance analyses of an expected dose-effect on outcome, particularly for AR + IVR participants. The 2:1 assignment strategy also fits our respective health system’s interest in maximizing the potential treatment benefits to study participants, which is important to increase cooperation among institutions in the study and helps build organizational interest in improving cessation services. We do not stratify recruitment on population characteristics other than race-ethnicity and gender. Stratification on factors determined during the patient interview, such as nicotine dependence, is not practical in a busy hospital setting. The additional complexity would add time to the patient encounter, potentially disrupt patient care, and jeopardize recruitment. Any variation in patient factors affecting quitting will be evaluated in the statistical analysis. Combining data across all CHART studies will also aid in the evaluation of quit predictors across sites.

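### The randomization reduces, but does not eliminate, the recruiter's ability to guess the next arm, because past assignments on a blocked 2:1 list are visible to the recruiter, most clearly at KP

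*Protocol article*

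**What the plan says.** All places are in the protocol article, Methods/Design.

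- **List.** The Randomization section gives each site 450 patients at 2:1 (300 to AR + IVR, 150 to UC), "using a predetermined randomization sequence with permuted blocks of randomly varying size". It adds: "The block size is masked from all except the data coordinating center (DCC) statistician and programmer". Envelopes are sealed and sequentially numbered, and the arm cannot be read from outside.
- **Claim.** From this the section concludes: "This strategy ensures balanced enrollment over time and eliminates the ability of the TTS to guess assignment prior to randomization".
- **Who sees the arms.** The TTS takes the next envelope once a patient passes prescreening, and opens it after consent and baseline. "Inside each envelope are two identical self-adhesive labels printed with the randomization number and treatment arm assignment". At KP "the TTS affixes one of the randomization labels to the" site's randomization log. At OHSU the label goes into the individual patient's research chart. At both sites the second label goes on the enrollment checklist sent to data entry.
- **Who recruits.** In-person screening and baseline assessment: "The TTS conducts face-to-face screening to confirm eligibility, assess interest in participation, conduct informed consent procedures". The same TTS completes the baseline assessment and randomizes.

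**The concern.** Masking the block size and varying it at random hides where a block ends. It does not hide what has already been assigned. Permuted blocks keep pulling the running count back to 2:1, so anyone who knows recent assignments in order knows something about the next one. Here the person with some or all of that knowledge also judges eligibility and interest at the bedside before opening the envelope. This would be so even if every envelope were handled perfectly and in order.

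The primary outcome is self-reported thirty-day abstinence, for which motivation is plausibly a strong predictor, and the TTS can gauge motivation before assignment. If more promising patients were enrolled when AR + IVR looked likely, the arms would differ at baseline. Model 1, the primary analysis, contains treatment only and would count that difference as a treatment effect.

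**Working it through.** **The plan's own figure.** The article gives no figure for predictability. The yardstick is the 8-point difference in the Power section (15% v 23%, 2:1, two-sided 0.05, 80% power), and its sample size reproduces. The pooled rate is (0.15 + 2 × 0.23)/3 = 0.2033.

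n(UC) = [1.960 × √(1.5 × 0.2033 × 0.7967) + 0.8416 × √(0.15 × 0.85 + 0.23 × 0.77/2)]² / 0.08² = (0.966 + 0.391)² / 0.0064 ≈ 288

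The total is 3 × 288 = 864, as stated. Predictability does not enter this calculation.

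**Inputs for predictability.** From the article: 2:1, 450 per site, permuted blocks of varying masked size. Assumed: five sets of block sizes (multiples of 3), each size in a set equally likely. Site lists of 450 were simulated, 800 per set.

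**Tally rule.** Let T = (number AR + IVR) − 2 × (number UC) so far. T < 0 means UC is ahead, and T > 0 means AR + IVR is ahead. The rule uses no knowledge of block sizes. With no history, P(next = AR + IVR) = 2/3 = 0.67.

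**Illustrative bias (assumed 5-point gap).** Give patients enrolled when UC is ahead a prognosis of +2.5 points, those enrolled when AR + IVR is ahead −2.5, and the rest 0. The difference between arms before any treatment is

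B = 2.5 × {[P(UC ahead | AR) − P(UC ahead | UC)] + [P(AR ahead | UC) − P(AR ahead | AR)]}

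For blocks 3/6 with a full tally: 2.5 × [(0.498 − 0.067) + (0.644 − 0.213)] = 2.5 × 0.862 ≈ 2.2 points. For 9/12/15: 2.5 × [(0.499 − 0.194) + (0.602 − 0.295)] = 2.5 × 0.612 ≈ 1.5 points.

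**Full ordered history visible**

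| Assumed blocks | P(AR + IVR next), UC ahead | P(AR + IVR next), AR + IVR ahead | B (points) |
|---|---|---|---|
| 3/6 | 0.94 | 0.40 | 2.2 |
| 3/6/9 | 0.90 | 0.43 | 1.95 |
| 6/9 | 0.88 | 0.45 | 1.8 |
| 6/9/12 | 0.86 | 0.47 | 1.7 |
| 9/12/15 | 0.84 | 0.50 | 1.5 |

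**Only a random half of the envelopes visible** (for example, two TTSs sharing a site, each knowing only their own openings)

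- Whole-study tally: about 0.68 with UC ahead and 0.65 with AR + IVR ahead; B about 0.2 points in every set.
- Tally of what was seen among the last five envelopes: 0.72-0.76 against 0.58-0.62; B 0.5-0.8 points.

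**How good a guess is.** Always guessing AR + IVR is right 66.7% of the time. With a full tally and unknown block sizes, guessing UC when T is 2 or more is right 75.5% (3/6), 73.8% (3/6/9) and 71.8% (6/9/12) of the time. Certainty about the next arm arises for about 11%, 4% and 2% of patients in those sets, and only for someone who knows the set of sizes, which is masked.

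**The case against.** The strongest reply is that randomly varying, masked blocks in sealed sequential envelopes are standard for an open-label behavioral trial, and that the larger figures need one recruiter to hold the complete ordered history. The article supports that only in part. It speaks of TTSs in the plural and has them initial the log. A cumulative arm log is described only at KP. At OHSU the label goes into single patient charts. This stands, and it is why the size must be given as a range reaching down to about 0.2 points.

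Other safeguards also count. Contact order is set by an algorithm. The fidelity review compares log, priority list, checklists, dates and times. Baseline measures of dependence and confidence, and an adjusted analysis that includes stage of readiness, cover part of the feared imbalance. So it would be wrong to say that nothing in the plan could reveal a problem. These measures limit the risk without removing it: the TTS still applies record exclusions, confirms eligibility and assesses interest. The review as described is aimed at deviations in assignment and sequence rather than at selective enrollment with envelopes used in order. Adjustment reaches only what was measured.

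A reader might infer that the TTS can predict the next arm at both sites, or that about a quarter of the 8-point target could be bias. The article does not support either. The tally shifts odds and seldom gives certainty. The top figure combines small blocks, full visibility and an unsourced 5-point gap acted on at most enrollments. The fixed 300:150 total per site informs only the last few envelopes.

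**Conclusion.** The claim of elimination is wrong on the article's own description; *reduces* is what the design delivers. The mechanism is clearest at KP, where the shared log carries number and arm. At OHSU it depends on how many TTSs share the work, which the article does not say.

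The effect on P(AR + IVR next) runs from slight (0.68 v 0.65) to marked (0.94 v 0.40). The illustrative bias runs from about 0.2 to 2.2 points against 8, depending on block sizes, visibility of past arms and the prognosis gap, all of which are assumed here. Withholding the block sizes is proper masking and no fault. There is no evidence that selection took place, and the sample size stands.

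**What to change.** 1. **Wording.** In the Randomization section, replace *eliminates* with *reduces, but does not eliminate*. No cost.
2. **KP log.** For unopened envelopes, enter only the randomization number on the site log, without the arm. The arm label continues to go on the enrollment checklist sent to data entry, so the fidelity review can still compare assignments. The cost is a small change in log handling while recruitment runs. The gain is partial, since each TTS still knows the arms they opened.
3. **Check.** Have the coordinating center, which knows the block sizes, compute for every envelope, including those already used, the probability of AR + IVR given the earlier assignments in its block (AR + IVR places left divided by all places left). It should then regress baseline predictors and, with treatment in the model, the primary outcome on that probability (Berger-Exner check) and report the result. This needs one extra analysis of data already held. It can detect selection but does not correct it.

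An unblocked list is not proposed: it would give up the plan's stated aim of balanced enrollment over time.
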